## Abstract

**Background:**

The Diabetes Manual is a type 2 diabetes self-management programme based upon the clinically effective 'Heart Manual'. The 12 week programme is a complex intervention theoretically underpinned by self-efficacy theory. It is a one to one intervention meeting United Kingdom requirements for structured diabetes-education and is delivered within routine primary care.

**Methods/design:**

In a two-group cluster randomized controlled trial, GP practices are allocated by computer minimisation to an intervention group or a six-month deferred intervention group. We aim to recruit 250 participants from 50 practices across central England. Eligibility criteria are adults able to undertake the programme with type 2 diabetes, not taking insulin, with HbA1c over 8% (first 12 months) and following an agreed protocol change over 7% (months 13 to 18). Following randomisation, intervention nurses receive two-day training and delivered the Diabetes Manual programme to participants. Deferred intervention nurses receive the training following six-month follow-up. Primary outcome is HbA1c with total and HDL cholesterol; blood pressure, body mass index; self-efficacy and quality of life as additional outcomes. Primary analysis is between-group HbA1c differences at 6 months powered to give 80% power to detect a difference in HbA1c of 0.6%. A 12 month cohort analysis will assess maintenance of effect and assess relationship between self-efficacy and outcomes, and a qualitative study is running alongside.

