### Sample size and rate of recruitment

We originally sought power of 90% (alpha = 0.05) to detect a 0.6% difference in individual patient HbA1c between intervention and control arms. Based on feasibility work, we estimated that the number of patients who have type 2 diabetes per recruited practice that meet the inclusion criteria would be an average of 80 so it would be reasonable for each practice to recruit and manage between 5–12 patients (expected mean number of patients = 10). Using an intra cluster correlation for HbA1c of 0.043 and allowing for 15% patient attrition and variability in clusters size gives an adjusted sample size of 212 in each arm. Allowing for an attrition rate of 10% for practices, we aimed to recruit a total of 46 practices, each willing to recruit up to12 patients. Because of the lower rate of patient recruitment in the first twelve months, we expected fewer patients per practice. We compensated for this by recruiting more practices. We estimated that with analysable data on five patients per practice in 50 practices the power of our study to detect a 0.6% difference would be 80% (accounting for between cluster correlation and variable cluster size as described above). This gives a lower power than we originally aimed for but was a realistic target.

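### The recruitment target of 250 equals the analysable number behind the 80% power, so the revised target carries no allowance for the protocol's own attrition rates

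*Protocol article*

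**What the plan says.** The abstract (Methods/design) gives a recruitment number, "We aim to recruit 250 participants from 50 practices across central England", and describes the primary analysis as "powered to give 80% power to detect a difference in HbA1c of 0.6" per cent.

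The section on sample size and rate of recruitment gives two calculations.

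- **Original.** The aim was 90% power at alpha 0.05 for a 0.6% difference, with ICC 0.043 and a mean of 10 patients per practice. Loss was built in at both levels: "allowing for 15% patient attrition and variability in clusters size gives an adjusted sample size of 212 in each arm", and then "Allowing for an attrition rate of 10% for practices" to reach 46 practices.
- **Revised.** After slow recruitment: "with analysable data on five patients per practice in 50 practices the power of our study to detect a 0.6% difference would be 80" per cent. The factors carried over are listed in a parenthesis: "accounting for between cluster correlation and variable cluster size as described above". Attrition is not among them. The section says openly that 80% is lower than first intended.

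The article gives no revised recruitment number above 250 and no revised practice number above 50.

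**The concern.** Five analysable patients in 50 practices is 250 analysable patients. The abstract gives the same 250 from the same 50 practices as the number to recruit, and attaches the same 80% to it. Both statements hold only with complete six-month HbA1c from every patient in every practice. The protocol did not expect that when it first sized the trial. It also notes, under practices and participants, that the eligible group now contains a greater share of people who attend reviews poorly, and six-month clinical outcomes are collected at a nurse review.

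At stake is the headline power for the primary comparison. The reduction from 90% to 80% is disclosed; any further reduction from attrition is not. A null result would be read against an 80% claim that the recruitment target does not support on the protocol's own allowances.

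**Working it through.** **Inputs from the protocol article.** Difference 0.6; alpha 0.05 (taken as two-sided); ICC 0.043; original 212 per arm at 90% power, including 15% patient attrition, mean cluster 10; practice attrition 10%; revised 50 practices × 5 analysable. Equal arms are assumed.

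**Not stated, so inferred or varied.** The HbA1c SD and the CV of cluster size.

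**Formulas.** Design effect DE = 1 + ((1 + CV²)m − 1) × 0.043. Effective n per arm = n/DE. SE = SD × √(2/effective n). Power = Φ(0.6/SE − 1.96).

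**Step 1: infer the SD (CV = 0).**
- From the original figure: analysable per arm = 212 × 0.85 = 180.2. With m = 10, DE = 1.387 and effective n = 129.9, so SD = 0.6 × √(129.9/2)/(1.96 + 1.2816) = 1.49. With m = 8.5 (10 × 0.85), DE = 1.3225 and SD = 1.53.
- From the revised figure: 125 per arm, m = 5, DE = 1.172, effective n = 106.7. The SD that gives exactly 80% is 0.6 × √(106.7/2)/(1.96 + 0.8416) = 1.56.

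**Step 2: reproduce the stated 80% with 250 analysable.** Power is 83.6% at SD 1.49, 81.8% at SD 1.53 and 80.0% at SD 1.56 (the last by construction). The stated figure therefore fits 250 patients analysed, with no loss.

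**Step 3: apply the protocol's losses to 250 recruited.**
- Patient loss only: 250 × 0.85 = 212.5 analysable, 106.25 per arm, m = 4.25, DE = 1.140, effective n = 93.2.
- Practice loss only: 45 practices × 5 = 225 analysable, 112.5 per arm, m = 5, DE = 1.172, effective n = 96.0.
- Both: 45 × 4.25 = 191 analysable, 95.6 per arm, DE = 1.140, effective n = 83.9.

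| Loss applied to 250 recruited | SD 1.49 | SD 1.53 | SD 1.56 |
|---|---|---|---|
| None | 83.6% | 81.8% | 80.0% |
| 15% of patients | 78.4% | 76.5% | 74.5% |
| 10% of practices | 79.6% | 77.7% | 75.7% |
| Both | 74.1% | 72.0% | 70.0% |

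**Step 4: vary the CV, in both the SD inference and the power.** With the SD back-solved from 212 per arm (m = 10), CV 0.5 gives 79.8% (patient loss) and 75.5% (both); CV 0.7 gives 81.0% and 76.8%. The no-loss power under that SD is then 84.6% and 85.5%, so the gain comes from a smaller inferred SD, not from tolerance of attrition. With the SD set to return the stated 80% at 250 analysable, CV 0.7 gives 75.0% and 70.5%.

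**Step 5: recruits needed for 250 analysable.** 250/0.85 = 294.1, so 295 for patient loss only. 250/(0.85 × 0.90) = 326.8, so 327 for both, from about 56 practices (50/0.90 = 55.6).

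**The case against.** Four points can be made on the other side.

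1. **The sample size section is right as it stands**, because it speaks of analysable data; only a one-line abstract turns 250 into a recruited count. Practices could also recruit up to 12 patients each, so five is not a cap. This is fair as to where the slip lies. But the abstract states a recruitment aim and attaches the 80% to it, the sample size section gives no larger number, and it expects fewer patients per practice. A ceiling of 12 is not an attrition allowance.

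2. **Practice loss may not apply.** The 10% is not defined as loss after patients are enrolled. It could cover practices that sign up and contribute nobody, and the 50 could be contributing practices. This stands. A reader might infer that power is simply 70–74%; the article does not support that as a single result, since it requires both losses on top of 250 enrolled.

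3. **The percentages rest on unstated inputs.** This stands too. The two ends of each range use different SDs, one of which returns about 84% rather than 80% before any loss, and the article says variable cluster size was accounted for without giving a CV. The equality of recruited and analysable numbers depends on none of this.

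4. **Baseline adjustment may restore the power.** Multiplying the SD by √(1 − r²) with an assumed r of 0.5 turns the 70.0% into about 82%; with patient loss only, r = 0.3 gives about 78–82%. So a reader should not conclude that the planned analysis is shown to fall short of 80%. Equally, the article gives no correlation and claims no such gain, and baseline outcome is only one of the covariates to be considered, subject to a 10% inclusion rule.

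**Conclusion.** The point holds as a mismatch between two stated numbers: the recruitment target equals the analysable number required for 80% power, and the protocol's own attrition allowances have dropped out of the revision. That part needs no assumption.

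The size does. At CV 0, with SD 1.49 to 1.56, two-sided alpha 0.05 and ICC 0.043, unadjusted power for 250 recruited is about 75–78% with patient attrition only and about 70–74% with practice attrition as well; a CV of up to 0.7 lifts the upper ends to about 81% and 77%. If the stated 80% at 250 analysable is taken at face value, every loss scenario examined falls below it, at about 70–76%. The documents do not establish 70–74% as the trial's power, nor that a baseline-adjusted analysis would miss 80%.

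**What to change.** In the abstract and the sample size section, give the recruited and the analysable numbers separately. Then do one of the following:

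- restate the unadjusted power for 250 recruited, about 70–78%, with the attrition rates, SD and cluster-size CV it assumes, and say whether the 10% practice loss applies to the 50 practices; or
- state the power for a baseline-adjusted analysis, with the assumed baseline-to-follow-up correlation and the same attrition assumptions.

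The cost is about two sentences and, on the first route, a less favourable stated power. Neither route needs extra patients. The figures of 295 and 327 recruits apply only if the team wishes to keep 80% unadjusted power by raising the target.

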**Discussion:**

This trial incorporates educational and psychological diabetes interventions into a single programme and assesses both clinical and psychosocial outcomes. The trial will increase our understanding of intervention transferability between conditions, those diabetes related health behaviours that are more or less susceptible to change through efficacy enhancing mechanisms and how this impacts on clinical outcomes.

## Background

### International health policy

The past decade has seen an international trend towards providing primary care based diabetes services with patient education and self-management at the forefront. The International Diabetes Foundation (IDF)[1] standards advocate that "implementation of diabetes education is learner-centred, facilitates cognitive learning, behaviour change and self-management". These are challenging goals for health care providers to uphold but nonetheless are being incorporated into national health policies. For example, shared decision making is a standard promoted in Finland [2], the Americas [3] and the Netherlands [4].

In the United Kingdom (UK), health professionals are expected to work with people living with diabetes to develop their confidence, skills and knowledge, engage in shared decision making and to provide theory-based structured education [5-7]. It has been proposed that such education should meet four criteria [8]: (i) have a structured, written curriculum (ii) have trained educators (iii) be quality assured, and (iv) be audited. The majority of people living with type 2 diabetes access education, information and support through primary care [9] which is currently structured, almost exclusively, around individual patient consultations. The potential of practice nurses to support individuals in structured patient self-management education within this existing, and valued, primary care structure needs to be built upon.

### Self-management interventions improve clinical outcomes

Psychological interventions for use in type 2 diabetes have been systematically reviewed and pooled trial results suggest they reduce HbA1c by a clinically significant 1% [10]. The need for research that combines psychological interventions with educational packages to understand the impact of psychological interventions on self-management behaviours has been recognised [11]. Hampson et al [12] reviewed behavioural interventions for adolescents with type 1 diabetes and found that only a minority of studies described interventions that were explicitly based on theories. The theoretically determined interventions, however, generated larger effect sizes than those that were atheoretical. Earlier systematic reviews of patient self-management training in long term conditions [13-15] concluded that collaborative self-management interventions, where people respond to clinical information and goal setting, represent the most effective self-management approaches for improving clinical outcomes. Together, these reviews suggest a need to explore theory-based self-management intervention development, involving biomedical feedback and goal evaluation.

### Self-efficacy theory

Improving an individual's self-efficacy is particularly important in long term disease self-management as it reflects capacity to carry out health related behaviours that are likely to improve outcome[16]. This parameter is based on social learning theory and reflects an individual's level of confidence in their ability to perform particular behaviours. Interventions to increase efficacy based on this theory, include four specific techniques of facilitating personal mastery, vicarious (observing others) learning, identifying distress and providing verbal persuasion. These have been shown to be powerful ways for people to learn new behaviours and activities. Enhancing self-efficacy in long term disease management has been shown to be associated with lower levels of health care consumption and improved psychosocial adjustment [17, 18, 19, 20].

### One to one education

The evidence for the effectiveness of group education is growing, [7,21] but group approaches do not suit everyone [22]. Randomised controlled trials of the Heart Manual [23,24], a home-based one-to-one secondary prevention programme for coronary heart disease, demonstrated findings that were at least equal to group approaches. Dalal & Evans [22] reported that the one to one Heart Manual was 11% more popular with primary care patients than the group alternative. It also had an 87% programme completion rate compared to the 33% completion rate of the group-based programme. The study found those over 60 years, the self-employed and those living in rural locations to particularly prefer an individual approach. Individual approaches and group-based self-management programmes may, therefore, be complementary. Both may be needed to engage the wide constituency of people requiring diabetes self-management education.

### The Diabetes Manual intervention

The Diabetes Manual, combining the three preceding strategies for improving outcomes in a single package, was developed at the University of Warwick in 2003–4, based on the Heart Manual. The development of a programme was prioritised in a needs assessment [25] and its subsequent development was informed by both lay and professional expert panels. Two focus groups of people with type 2 diabetes confirmed that the penultimate draft of the Diabetes Manual had face validity. The Diabetes Manual programme incorporates self-efficacy enhancing text and activities and has been designed to enable patients to gain confidence and skills quickly and progressively in the management of their diabetes[26]. The programme has five components, i) two-day training for nurse to deliver the programme ii) 12 week patient manual iii) relaxation audiotape iv) frequently asked questions audiotape for patient and carers v) telephone support from nurse in weeks 1,5 and 11. The Diabetes Manual is designed to be offered to patients during primary care consultations with GPs and practice nurses and therefore is intended to have high availability to its target population. It is able to meet the UK standards for structured education in diabetes [8]. This paper discusses a trial that is now underway to test the effectiveness of the Diabetes Manual programme.

## Trial objectives

### Primary objective

To determine the efficacy of the Diabetes Manual in type 2 diabetes for improving glycaemic control at 6-months compared with usual care and to determine the persistence of effect at 12 month in the intervention group.

### Secondary objectives

To determine the efficacy of the Diabetes Manual in modifying the following risk factors for cardiovascular disease: total serum cholesterol; HDL cholesterol; blood pressure and BMI. To reduce anxiety and improve quality of life and self-efficacy.

## Methods/design

The Diabetes Manual trial is a two-arm RCT, clustered by GP practice with an intervention arm and a control arm in which intervention is deferred and delivered at six-months. As the practice nurse is the target of the educational intervention, the design appropriately takes the practice as the unit of randomisation. The trial is being managed by the Centre for Primary Health Care Studies, University of Warwick, UK. Ethical approval was granted by the Northern and Yorkshire Multi-centre Research Ethics Committee in June 2004.

### Practices and participants

GP practices from three Strategic Health Authorities in central England have been recruited. Practice eligibility is i) employment of a practice nurse who has undertaken post-registration diabetes care training and ii) use of a laboratory in which HbA1c ranges and assays are DCCT aligned [27] determined and stable. Patient eligibility criteria are adults with type 2 diabetes, not taking insulin and able to read and write English. During the first 12 months of the study, eligible patients had a most recent HbA1c over 8%. We experienced low recruitment over this period as trial commencement concurred with the implementation of a payment linked quality improvement policy [28] during which time GPs have become more aggressive in the prescribing of oral hypoglycemic agents and insulin in an attempt to reduce each patient's HbA1c to below the maximum payment threshold of 7.4%. This has resulted in considerably fewer patients than anticipated meeting the eligibility criteria. It also means that eligible patients include a greater proportion of those for whom more aggressive pharmacological management was not working either due to poor attendance at reviews, complex diabetes management situations or treatment concordance issues. One year into the trial a protocol change was agreed by the investigators, funders and the research ethical committee to enhance patient recruitment by reducing the patient eligibility to a minimum of HbA1c 7%.

### Screening eligibility

Participating practices identified eligible patients from practice registers and a researcher visited to collect aggregated data for all eligible patients and generate a random ordered recruitment list [figure 1]. Aggregated, anonymised HbA1c, blood pressure (BP), body mass index (BMI) and basic demographic data of the eligible practice populations were collected prior to recruitment to allow any difference between the actual study participants and the eligible population to be identified. Patients were invited to participate by the nurse according to the random order list. This ensured that patients were invited consecutively on the grounds of eligibility rather than on the grounds of anticipated concordance by the practice nurse. The list was followed until 12 patients were recruited or the list was exhausted. All patients were recruited prior to practice cluster randomisation.

**Figure 1 F1:**
[figure not shown]
Flowchart of trial from recruitment to randomisation.

### Baseline assessment

Baseline clinical assessment was conducted by the practice nurse prior to randomisation during an additional diabetes review. Blood samples for HbA1c assessment, total and HDL cholesterol were taken by the nurse and analysed outside the practice by the DCCT aligned [27] laboratory blinded to practice or patient group allocation. A self-completion booklet of questionnaires consisting of demographic questions, the problem areas in diabetes scale (PAID) [29], the diabetes management self-efficacy scale (DMSES) [30] and the diabetes self-care activities measure [31] was given to the patient by the nurse at baseline for return in replied paid envelope to the research team. Process data consisted of the diabetes self-care activities scale [31] and prescribed medication collected by the practice nurse during clinical assessment. Demographic data includes age, gender, net weekly income, highest educational qualification, ethnicity and duration of diabetes.

### Outcome assessment

Follow up for all measures is at six months post randomisation for both arms and 12 months post randomisation for the intervention arm to assess maintenance of effect on all measures. Six and 12-month clinical assessment is carried out by the practice nurse during a diabetes review. Psychosocial measures are collected by self-completion patient postal questionnaire.

### Group allocation

Following patient baseline data collection, practices were minimised [32] into intervention and control arms according to mean HbA1c of recruited patients, practice self-assessed quality of diabetes care indicators [28] and the number of individuals recruited [figure 2]. Computer-aided minimisation was undertaken by a statistician blind to practice identity. All members of the research team who will be inputting, analysing and interpreting both qualitative and quantitative data are blind to the group allocation of practices and participants. The nurse trainer, one research fellow and one secretary remain unblinded to ensure effective communication and support between the research team, the practices and the participants regarding training events and follow-up data collection.

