### Statistical analysis

Data is double entered and discrepancy checks carried out with source data. To account for clustering by practice, primary and secondary outcomes will be analysed using population averaged models with robust standard errors (using generalised estimating equations). Patient and practice level covariates thought to be related to outcome, including practice self-assessed quality of diabetes care indicators [28], geographical location of practice, level of patient outcome at baseline (where available), and patient age, gender, education and socio-economic status will be considered for incorporation in the analysis. Covariates will be included if they show a strong (α<10%) relationship with outcome. We will also include a covariate representing whether the practice was recruited before or after the change in protocol relating to HbA1c levels. To detect the presence of any significant differences in effect between sub-groups, we will fit first order interaction terms for interactions between intervention and the following factors which represent the sub-groups of interest: laboratory used for blood sample analysis, patient age and educational attainment. Separate models will also be fitted for the separate subgroups, but these results will be exploratory rather than definitive. The questions we aim to explore in the subgroup analyses are: Is the effect on HbA1c different for patients recruited before and after the protocol change or for patients in different age groups? Is any effect on self-efficacy different for older and younger patients or by educational attainment?

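### None of the three minimisation factors is guaranteed a place in the models, so the standard error is too large for any prognostic factor that is left out

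*Protocol article*

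**What the plan says.** Under Group allocation, the protocol article minimises practices "according to mean HbA1c of recruited patients, practice self-assessed quality of diabetes care indicators [28] and the number of individuals recruited".

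Under Statistical analysis, primary and secondary outcomes are analysed with "population averaged models with robust standard errors (using generalised estimating equations"), to allow for clustering by practice. The candidate covariates are described as "Patient and practice level covariates thought to be related to outcome, including practice self-assessed quality of diabetes care indicators [28], geographical location of practice". The list goes on to the patient's baseline level of the outcome (where available), age, gender, education and socio-economic status. These "will be considered for incorporation in the analysis", and the rule for keeping them is "Covariates will be included if they show a strong (α<10%) relationship with outcome".

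One covariate is included without condition: "We will also include a covariate representing whether the practice was recruited before or after the change in protocol". It was not a minimisation factor.

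**The concern.** Minimisation restricts how far the arms can differ on the factors it balances. If such a factor predicts outcome, the treatment estimate varies less from one allocation to another than under simple randomisation. A model that leaves the factor out still counts its variance in the standard error. The interval is then too wide and the test rejects too seldom.

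Whether an allocation factor belongs in the model follows from the design, not from its p-value in the trial data. The article separates a forced covariate from screened ones and puts the allocation factors on the screened side or leaves them unnamed. This is therefore a stated rule, not detail left to a fuller analysis plan.

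Precision and a correct error rate are at stake. The trial has already accepted a fall in planned power from 90% to 80%, so precision that the allocation has made available should not depend on a screen.

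**Working it through.** **1. Allocation against analysis**

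| Minimisation factor | HbA1c model | Other outcomes |
|---|---|---|
| Practice mean HbA1c | Candidate through the patient's baseline HbA1c; 10% screen | Not a named candidate; the baseline term is that outcome's own level |
| Quality indicators | Candidate; 10% screen | Candidate; 10% screen |
| Number recruited | Not named | Not named |

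**2. Size of the effect when a factor is left out**

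The article gives no figure for how much variance the factors explain. Let R² be the share of practice-mean outcome variance explained by the balanced, omitted factors, over an assumed range of 4%, 9% and 25%. Assume complete balance, a two-sided 5% test (the article gives alpha = 0.05 without sidedness) and 80% as the base power, the article's revised figure. Write f = 1/√(1 − R²).

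- Ratio of reported to true standard error: f.
- True type I error: 2 × (1 − Φ(1.96 f)).
- Power with the factors left out: the reported standard error gives a mean test statistic of 2.80, but the true spread is smaller by the factor f. Power is Φ((2.80 − 1.96) f) = Φ(0.84 f).
- Power with the factors included: Φ(2.80 f − 1.96).

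| R² | f | Type I error | Power, left out | Power, included | Forgone (points) |
|---|---|---|---|---|---|
| 4% | 1.021 | 4.5% | 80.5% | 81.6% | 1.1 |
| 9% | 1.048 | 4.0% | 81.1% | 83.6% | 2.5 |
| 25% | 1.155 | 2.4% | 83.4% | 89.9% | about 6.5 |

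**3. How likely omission is under the 10% screen**

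- Baseline HbA1c in the HbA1c model: with an assumed baseline-outcome correlation of 0.5 and about 250 patients, t = 0.5 × √(248/0.75) ≈ 9.1, ignoring clustering. It would almost surely be kept.
- A practice-level factor: with 50 practice means (48 df), the two-sided 10% cut-off is t = 1.677, so the observed R² must exceed 1.677²/(1.677² + 48) ≈ 5.5%. A named factor whose true R² is 4%, 9% or 25% passes about 40%, 70% or 99% of the time.
- Put another way, a practice factor worth 0.3% HbA1c, with a standard error of about 0.17, passes with probability about Φ(0.3/0.17 − 1.645) ≈ 0.55.

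**4. Simulation of the HbA1c model**

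Fifty practices of about five patients were minimised on three binary factors and analysed by independence GEE with an uncorrected robust standard error, 1,500 trials per scenario. Assumptions: SD 1.5, baseline-outcome correlation 0.5 to 0.6, practice-factor effects 0 to 0.5% HbA1c. The intracluster correlation of 0.043 is the article's. The article gives no SD; its 212 per arm implies about 1.44 to 1.53.

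| Factors in model | Mean SE | True SD | Type I error | Power for 0.6% |
|---|---|---|---|---|
| None | 0.204–0.229 | 0.187–0.198 | 2.5–4.5% | 75–82% |
| Baseline HbA1c only | 0.176–0.194 | 0.170–0.184 | 3.1–5.7% | 88–90% |
| All three | 0.159–0.173 | 0.162–0.185 | 5.5–6.1% | 90–95% |

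Scenario by scenario, the standard error is 3% (0.204/0.198) to 22% (0.229/0.187) too large with no factor in the model. With baseline HbA1c alone the excess runs from none to 14% (0.194/0.170), the top figure arising when both practice factors are worth 0.5% HbA1c. With all three the uncorrected robust standard error is slightly too small.

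**The case against.** A reader might infer that the standard error simply ignores the balance created at allocation. The article does not support that. Two of the three factors are named candidates, and the screen tends to keep what predicts outcome. In the HbA1c model baseline HbA1c would almost surely stay, so most of the balance would be used. The 25% row would almost never arise for a single named factor. This stands, and it limits the point for the primary outcome.

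A reader might also infer that number recruited is excluded. The candidate list opens with the word *including*, so it is not closed and the factor is unnamed rather than ruled out. Nothing in the article says that it predicts HbA1c at six months. If it does not, leaving it out costs nothing. This stands too.

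Nor does the omission cut the stated 80% power. The sample-size section mentions clustering and variable cluster size but no covariate adjustment, so what is lost is a possible gain. Leaving factors out errs in the conservative direction and adds no false-positive risk.

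Two things remain after these concessions. For a practice-level factor of moderate strength, the screen is close to a coin toss, so the model and its standard error depend on the data. And the reassurance about baseline HbA1c applies only to the HbA1c model: for cholesterol, blood pressure, BMI and self-efficacy the named baseline term is that outcome's own.

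**Conclusion.** The point holds in a limited form. The article minimises on three factors and guarantees none of them in the analysis. For any balanced factor that predicts outcome and is left out, the standard error is too large and the test conservative. Over an assumed 4% to 25% of practice-mean variance explained, the overstatement is about 2% to 15%, type I error is about 4.5% to 2.4%, and about 1 to 6.5 points of power are forgone. These figures assume certain omission and complete balance. They are upper limits over that range for the HbA1c model. The article gives no data on how strongly the practice-level factors predict any outcome, so the actual size cannot be fixed from it. This is a worthwhile improvement, not a threat to the validity of a positive result.

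**What to change.** State in the analysis section that baseline HbA1c, the quality-indicator score and number recruited enter every primary and secondary model whatever their p-values, together with the outcome's own baseline level where available. State that the 10% screen does not apply to them.

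State also that the robust standard error carries a small-sample correction for about 50 clusters. This belongs with the change, because forcing in all three factors with an uncorrected robust standard error gave 5.5% to 6.1% type I error in the simulation.

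The cost is a few sentences and a few practice-level degrees of freedom out of about 50.
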